### Data collection

Assessment of clinical endpoints will take place at hospital visits during the intake, pre-ablation and the follow-up consultations at 3 and 12 months after ablation. Quality of life data will be collected using digital questionnaires at intake, pre-ablation, 3 months after ablation and 12 months after ablation.

An overview of the study procedures is displayed in Table 3.

**Table 3 Tab3:** Study procedures

Study procedure	Intake	Pre-ablation (only in interventional group)	3 months after ablation	12 months after ablation
Assessment of clinical history and clinical endpoints	x	x	x	x
Physical examination including blood pressure and weight	x	x		x
12-lead ECG	x		x	
Laboratory test	x	x		x
Quality of life using EuroQol-5D, AFEQT, Treatment Burden Questionnaire	x	x	x	x

*ECG* electrocardiogram

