### Endpoints

The primary composite endpoint of the study is the number of hospitalizations for re-ablation and cardioversion from baseline to 12 months after ablation. The conditions for performing a re-ablation and cardioversion are explained above.

Secondary endpoints are the number of hospitalizations for re-ablation, the number of cardioversions, the number of cancelled ablations because of overall symptom reduction, mortality, number of strokes, acute ischemic events, or hospitalizations for heart failure at 12 months after ablation.

Further secondary endpoints include change in weight, blood pressure and laboratory tests at baseline, after the lifestyle intervention (for the intervention group) and at 1 year after ablation. Furthermore, ablation success is determined at 12 months after ablation. The ablation is considered to be successful when patients can stop their antiarrhythmic drugs after 3 months, without having recurrence of symptomatic arrhythmias urging for re-ablation. The elaborate lifestyle changes might negatively affect treatment burden. Treatment burden is the perception of cumulative work a patient has to perform to manage their health, and should, therefore, be limited. Therefore, further secondary endpoints include the change in quality of life and treatment burden from baseline to before ablation, at 3 months, and 12 months after ablation. The patient’s general quality of life will be assessed with the Dutch version of the EuroQol-5D questionnaire. This questionnaire includes 5 health-state measures and is suitable to determine quality-adjusted life-years for a cost–utility analysis [31]. AF-specific quality of life is assessed with the Dutch version of the AF effect on Quality of Life Survey (AFEQT). This questionnaire is suitable for describing AF-related symptoms [32]. Treatment burden will be evaluated with a Dutch translation of the Treatment Burden Questionnaire.

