### Statistical analyses

Descriptive statistics will be used to report baseline characteristics of the study population. The primary and secondary endpoints can occur during the entire participation period, which is from baseline to ablation (in the intervention group during the risk treatment; in the control group when patients await the ablation) and in 12 months after the ablation. The different pre-ablation durations amongst patients lead to different study participation periods. Therefore, the number of events will be normalized using the participation period and will be reported in numbers per year (the event rate). The clinical hypothesis that the intervention group will have a lower event rate will be tested by fitting a Poisson regression model to the event data and testing the effect of the intervention group using a Wald test. Results will be reported in terms of incidence risk ratios with accompanying 95% confidence intervals. The primary analysis will be on an intention-to-treat basis. Subgroup analyses will be performed on the primary endpoint. Covariates of interest in this study include gender, age, type of AF (paroxysmal vs. persistent) and number and extent of the respective modifiable risk factors as defined in Table 2.

The secondary endpoints will be analysed by means of chi-squared test or Fisher’s exact test depending on the number of occurrences. Changes in weight and blood pressure will be compared using the appropriate test (unpaired *t* test or Mann–Whitney *U* test), depending on the distribution of data. Laboratory tests will be analysed for differences by fitting linear mixed models to the data.

A cost-effectiveness analysis will be included, covering incremental cost-effectiveness ratio (ICER) and an evaluation of change in patient value, using the EuroQol-5D and AFEQT questionnaires and healthcare-related costs of intervention. Differences in medical hospital costs for both study groups will be compared using the appropriate statistical test (unpaired *t* test or Mann–Whitney *U* test), depending on the distribution of data. Cost savings associated with the study intervention will be calculated by subtracting the cost of the intensive treatment from the cost of the conventional treatment. The completed EuroQol-5D, AFEQT and TBQ questionnaires will be analysed for differences between treatment groups at different moments by fitting linear mixed models to the data.

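### Table 3 confines the pre-ablation questionnaires to the intervention arm, contradicting the text; if the table is followed, the pre-ablation comparison of quality of life and treatment burden has no control data.

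*Protocol article*

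**What the plan says.** All references are to the Methods of the protocol article.

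- **Data collection, Table 3.** The second column is headed "Pre-ablation (only in interventional group". It is ticked for clinical history and clinical endpoints, physical examination, laboratory test, and the row "Quality of life using EuroQol-5D, AFEQT, Treatment Burden Questionnaire".
- **Data collection, text above the table.** "Quality of life data will be collected using digital questionnaires at intake, pre-ablation, 3 months after ablation and 12 months after ablation". For events: "Assessment of clinical endpoints will take place at hospital visits during the intake, pre-ablation and the follow-up consultations at 3 and 12 months after ablation". Neither sentence is limited to one arm.
- **Endpoints.** A secondary endpoint is "the change in quality of life and treatment burden from baseline to before ablation, at 3 months, and 12 months after ablation", again with no arm limit. A few lines earlier, the intermediate measurement of weight, blood pressure and laboratory values is expressly confined to the intervention group.
- **Statistical analyses.** The three questionnaires "will be analysed for differences between treatment groups at different moments by fitting linear mixed models to the data".
- **Primary endpoint (Endpoints).** It is "the number of hospitalizations for re-ablation and cardioversion from baseline to 12 months after ablation". Statistical analyses confirms that the controls' waiting period counts.

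**The concern.** The column header removes control data that a named secondary endpoint and its between-arm analysis need.

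Treatment burden is measured because the authors fear that the lifestyle programme may worsen it (Endpoints). That programme runs before ablation: three to five in-person nurse appointments plus further consultations by risk factor, for up to 6 months (Lifestyle interventions). Without a control value before ablation, the first controlled comparison of burden comes 3 months after ablation, when this phase is over. A change within the intervention arm alone cannot separate the effect of the programme from the effect of waiting for ablation.

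EuroQol-5D also supplies the utilities for the cost-utility analysis, so an unequal measurement schedule carries over into the quality-adjusted life-years.

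The same column schedules an endpoint assessment before ablation in one arm of an open-label trial, in a period during which primary events count in both arms.

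**Working it through.** The plan states no figure on this point, so the check compares the passages and counts what each schedule would deliver.

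**1. Is the restriction intended for the questionnaires?**

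| Item | Endpoints | Data collection text | Table 3, pre-ablation |
|---|---|---|---|
| Weight, blood pressure, laboratory | intervention arm only | not listed separately | intervention arm only |
| Quality of life, treatment burden | no arm limit | no arm limit (quality of life) | intervention arm only |
| Clinical endpoints | counted from baseline, both arms | no arm limit | intervention arm only |

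The header agrees with the text in the first row and conflicts with it in the other two. Where the authors want an arm restriction in the Endpoints section, they write one.

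**2. Questionnaire sets under each reading.** Sample size gives 150 patients and Trial design gives 1:1 allocation, so 150 / 2 = 75 per arm, ignoring dropout.

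- Text: 150 × 4 = 600 sets.
- Table 3: 75 × 4 + 75 × 3 = 525 sets.
- Difference: 600 − 525 = 75 sets, all in one cell (control, pre-ablation), which holds 0 of 75.

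**3. Contrasts lost.** Three questionnaires × three post-baseline times = 9 between-arm contrasts. The pre-ablation time accounts for 3 × 1 = 3 of them.

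**4. Can the analysis recover them?**

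- *Mixed model.* With a separate arm effect at each time, the control mean before ablation has no observations and is not identified. A model that forces a common arm effect or a straight line over time would return a number, but that number would come from the assumption and not from data.
- *Multiple imputation.* If the unscheduled control values were treated as missing, 75/150 = 50% would be missing at that time, which is above the article's 5% threshold for imputing. Imputation would have to borrow the relation between the pre-ablation value and the other values entirely from the intervention arm. It would thus assume how the two arms compare, which is the question being asked.

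**5. Utilities.** Under Table 3 the intervention arm has four utility points (intake, pre-ablation, 3 and 12 months) and controls have three. In the intervention arm the pre-ablation period can reach 6 / (6 + 12) = 33% of participation. The controls' waiting time is not stated. Their utility over that wait would be interpolated from intake to 3 months after ablation.

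**6. Primary endpoint.** Table 3 gives scheduled endpoint assessments at intake, 3 and 12 months to both arms, and one more before ablation to the intervention arm only. The share of control events that would be missed without that contact is not stated and cannot be derived.

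**The case against.** **The header may be a slip.** It suits the physical examination and laboratory rows, and a digital questionnaire needs no visit. If the text governs in practice, controls do complete the pre-ablation set and nothing is lost. This stands: the contradiction is certain, while the consequences hold only if the table is followed. It does not remove the need to reconcile the passages, because sites work from the schedule and a control who has passed ablation cannot supply the value later.

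**Burden is still compared at 3 and 12 months.** True. The documents also do not say that burden peaks before ablation, and the point does not need that. It needs only that the programme runs then.

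**The primary endpoint.** A reader might infer that control events before ablation go uncounted, that cancelled ablations are detected differently by arm, or that the rate ratio is shifted by some definite percentage. The documents do not support these readings:

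- Clinical history and endpoints are assessed at 3 and 12 months in both arms, so earlier hospital admissions can be picked up retrospectively.
- Patients in both arms are referred from other hospitals (Trial design), so outside cardioversions are not peculiar to controls.
- Counselling on cancellation is described without an arm limit, controls see the cardiologist (Usual care), and a single ablating centre would know which ablations it cancelled.
- No figure in the documents allows a shift to be calculated.

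What remains is one extra scheduled check in one arm.

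**Timing.** A control measurement just before ablation may fall at a different time since randomisation than in the intervention arm. Statistical analyses itself notes that pre-ablation durations differ. This is a fair point, and the fix has to deal with it.

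**Conclusion.** The concern holds as an internal contradiction with a conditional consequence. The Table 3 header conflicts with the Data collection text, with the secondary endpoint of change to before ablation, and with the between-arm questionnaire analysis.

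If the table is followed, no control has a pre-ablation EuroQol-5D, AFEQT or Treatment Burden Questionnaire value. Three of nine between-arm contrasts are then not estimable from observed data, and the cost-utility analysis rests on four utility points against three. These counts assume 75 patients per arm and the schedule exactly as tabulated.

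For the primary endpoint the consequence is minor: unequal ascertainment of unknown size in an open-label trial. It is not a missing endpoint.

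**What to change.** 1. Remove the arm restriction from the questionnaire and clinical-endpoint rows of Table 3, so that table, text, endpoint and analysis agree. Keep the pre-ablation examination and laboratory tests in the intervention arm only, as Endpoints states.
2. Send controls the same three digital questionnaires shortly before the planned ablation. In both arms, where the ablation is cancelled, send them at that decision.
3. At that contact, record cardioversions since randomisation on the same form in both arms, including any done at a referring hospital.
4. Record time since randomisation at each questionnaire, and use it in the mixed model and the utility calculation, because waiting times may differ by arm.
5. If control data can no longer be collected, describe the pre-ablation change within the intervention arm only and begin the between-arm comparison at 3 months.

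The cost is one extra digital questionnaire set and a short event form for about 75 controls. The downside is a small reporting burden for them. No clinical management changes.

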### Statistical analyses

Descriptive statistics will be used to report baseline characteristics of the study population. The primary and secondary endpoints can occur during the entire participation period, which is from baseline to ablation (in the intervention group during the risk treatment; in the control group when patients await the ablation) and in 12 months after the ablation. The different pre-ablation durations amongst patients lead to different study participation periods. Therefore, the number of events will be normalized using the participation period and will be reported in numbers per year (the event rate). The clinical hypothesis that the intervention group will have a lower event rate will be tested by fitting a Poisson regression model to the event data and testing the effect of the intervention group using a Wald test. Results will be reported in terms of incidence risk ratios with accompanying 95% confidence intervals. The primary analysis will be on an intention-to-treat basis. Subgroup analyses will be performed on the primary endpoint. Covariates of interest in this study include gender, age, type of AF (paroxysmal vs. persistent) and number and extent of the respective modifiable risk factors as defined in Table 2.

The secondary endpoints will be analysed by means of chi-squared test or Fisher’s exact test depending on the number of occurrences. Changes in weight and blood pressure will be compared using the appropriate test (unpaired *t* test or Mann–Whitney *U* test), depending on the distribution of data. Laboratory tests will be analysed for differences by fitting linear mixed models to the data.

A cost-effectiveness analysis will be included, covering incremental cost-effectiveness ratio (ICER) and an evaluation of change in patient value, using the EuroQol-5D and AFEQT questionnaires and healthcare-related costs of intervention. Differences in medical hospital costs for both study groups will be compared using the appropriate statistical test (unpaired *t* test or Mann–Whitney *U* test), depending on the distribution of data. Cost savings associated with the study intervention will be calculated by subtracting the cost of the intensive treatment from the cost of the conventional treatment. The completed EuroQol-5D, AFEQT and TBQ questionnaires will be analysed for differences between treatment groups at different moments by fitting linear mixed models to the data.

A *p* value < 0.05 will be considered statistically significant and all analyses will be performed using SPSS 29 (IBM SPSS Statistics 29.0, Chicago, IL, USA). We will use complete case analysis when the percentage of missing data is less than 5%. Otherwise, we will use multiple imputations by full conditional specification.

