## Methods

### Trial design

The POP study is a prospective, open-label, single centre, investigator-initiated, randomized controlled clinical trial (NCT05148338). Eligible patients referred for catheter ablation by other cardiologists in non-interventional hospitals will be randomly assigned in a 1:1 ratio to usual current temporary care or an elaborate lifestyle intervention. If a patient experiences a major reduction in AF symptoms during the pre-procedural work-up, the cardiologist will counsel the patient whether the ablation should be cancelled. Patients from both study groups will undergo a PVI according to common clinical practise. After the ablation or from the moment of the decision of the cancellation of ablation, patients will be followed for 12 months. Follow-up visits will be performed at 3 and 12 months after ablation and consist of a physical examination next to laboratory tests and quality of life questionnaires. A detailed study flow chart is shown in Fig. 1. The trial is non-blinded, since blinding is not possible, given that the treating physician is involved in the multidisciplinary team.

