### Study population

The study will enrol patients with paroxysmal or persistent AF referred for their first catheter ablation. Detailed inclusion and exclusion criteria are displayed in Table 1.

**Table 1 Tab1:** Inclusion and exclusion criteria

Inclusion criteria	Exclusion criteria
Age: 18–75 years Paroxysmal or persistent (shorter than 1 year) AF Referral for first catheter ablation At least one of the following risk factors: BMI ≥ 27 kg/m^2^ LDL-cholesterol > 2.6 mmol/L or total cholesterol > 5.0 mmol/L Hypertension (blood pressure > 130/90 mmHg) Diabetes mellitus with HbA1c ≥ 53 mmol/mol Active smoking Alcohol use > 14 equivalent units of alcohol/week Informed consent	Long-standing persistent AF (persistent for more than 1 year) Permanent AF Asymptomatic AF Prior catheter ablation Paroxysmal AF consisting of one episode with a reversible cause (e.g., fever, surgery, thyroid crisis, ischemic) Severe valvular heart disease Prior or soon foreseen implantation of cardiac device, such as pacemaker or internal cardioverter defibrillator Acute coronary syndrome < 3 months before inclusion Unstable heart failure NYHA class IV, or heart failure necessitating admission < 3 months before inclusion Cardiac surgery < 3 months before inclusion or planned cardiac surgery Malignancy Life expectancy < 1 year Pregnancy

*AF* atrial fibrillation, *BMI* body mass index, *LDL* low-density lipoprotein, *HbA1c* glycohemoglobin, *NYHA* New York Heart Association

The study will be conducted in accordance with the declaration of Helsinki, the good clinical practice, and the applicable regulatory requirements [29]. The locally appointed medical ethics committee has approved the research protocol. All participants will be informed by the investigator and are required to give their written informed consent prior to enrolment.

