### Post-ablation care

Patients of either treatment group will visit the outpatient clinic at 3 months after ablation. At this point, the treating physician will stop any current antiarrhythmic medication. If the patient does not experience any symptoms after ablation, no additional rhythm assessment will be performed, since this will not have therapeutical consequences. In symptomatic patients, arrhythmias will be objectivated with electrocardiogram or multiple holter assessments. If an arrhythmia is confirmed on electrocardiogram or holter after 3 months after the index ablation, patients are offered to recontinue antiarrhythmic medication and to undergo a repeat ablation. Furthermore, patients suffering from persistent AF will undergo cardioversion.

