### Sample size

The number of hospital admissions in the control group is estimated as 1.0 per patient per year [33, 34]. The proposed intervention is expected to reduce the primary endpoint with 30%. Taking the pre-ablation period into account, in the intervention group, we expect an overall event rate of 0.75 per patient per year. Assuming a balanced design with equal allocation of patients to the two groups, the minimum sample size to achieve an 80% power with 5% Type I error on the primary analysis is 144 (72 per treatment group). A total of 150 patients will be enrolled in this study, taking dropouts into account.

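### The article does not say whether AF type, a likely predictor of the primary event rate, is a term in the primary Poisson model

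*Protocol article*

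**What the plan says.** Both AF types are eligible: "The study will enrol patients with paroxysmal or persistent AF referred for their first catheter ablation" (Study population). The primary endpoint is "the number of hospitalizations for re-ablation and cardioversion from baseline to 12 months after ablation" (Endpoints), and that section refers back to the preceding text for the conditions under which each procedure is done. The preceding text on cardioversion is in Post-ablation care: "Furthermore, patients suffering from persistent AF will undergo cardioversion".

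The primary analysis is described as "fitting a Poisson regression model to the event data and testing the effect of the intervention group using a Wald test" (Statistical analyses). Only the intervention effect is named there. Later in the same paragraph come "Subgroup analyses will be performed on the primary endpoint" and then "Covariates of interest in this study include gender, age, type of AF (paroxysmal vs. persistent", followed by the modifiable risk factors. Nothing says whether the listed covariates are terms in the primary model, define subgroups, or both.

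**The concern.** One of the two components of the endpoint is linked, by the article's own description, to persistent AF. A patient's AF type at entry therefore probably predicts how many primary events that patient contributes. If AF type is left out of the model, two things follow.

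- In the one trial that is run, a chance difference between arms in the share with persistent AF moves the observed rate ratio.
- A plain Poisson Wald test sets the variance equal to the mean, so its standard error does not allow for the spread of rates between the two types.

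The wording also leaves both an adjusted and an unadjusted primary result consistent with the plan. In an open-label trial it is better that this choice is fixed in writing before the data are seen.

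**Working it through.** **Inputs from the article.** 150 patients at 1:1, so 75 per arm. The control rate is given by "The number of hospital admissions in the control group is estimated as 1.0 per patient per year". The planned intervention rate is 0.75, so the planned rate ratio is 0.75. Follow-up is 12 months after ablation plus a pre-ablation period, which is at most 6 months in the intervention arm.

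**Inputs assumed.** The article gives no AF-type mix or type-specific rates, so there is no figure of its own to reproduce on this point. Assumed:
- share persistent p = 0.3 to 0.5
- persistent-to-paroxysmal rate ratio k = 1.5 to 3
- allocation that does not balance AF type
- participation of 1.25 years (control) and 1.5 years (intervention), mean 1.375, with an average rate of 1.0 per year

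**Step 1: size of chance imbalance.** SD of the between-arm difference in share persistent = √(2p(1−p)/75).
- p = 0.3: √(0.42/75) = 0.075
- p = 0.5: √(0.50/75) = 0.082

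**Step 2: shift in the observed rate ratio.** For an imbalance d split evenly around p, with no treatment effect, the ratio is [1+(k−1)(p+d/2)] / [1+(k−1)(p−d/2)]. Example: p = 0.4, k = 2, d = 0.08 gives 1.44/1.36 = 1.059.

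**Step 3: type I error of the plain Wald test.** With v the variance of the patient rates scaled to mean 1, the dispersion is 1 + 1.375v, and the two-sided error is 2[1−Φ(1.96/√dispersion)]. Example: p = 0.4, k = 2 gives v = (0.6+0.4×4)/1.4² − 1 = 0.122, dispersion 1.168, error 7.0%.

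Ranges over p = 0.3 to 0.5:

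| k | Shift at 1 SD | Shift at 1.96 SD | Type I error |
|---|---|---|---|
| 1.5 | 1.033–1.034 | 1.066–1.068 | 5.6–5.7% |
| 2 | 1.056–1.059 | 1.113–1.120 | 6.8–7.0% |
| 3 | 1.085–1.098 | 1.174–1.202 | 9.1–10.4% |

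At the 95% limit, a true 0.75 would be seen as 0.75×1.07 = 0.80 to 0.75×1.20 = 0.90, or in the other direction as 0.75/1.07 = 0.70 to 0.75/1.20 = 0.63.

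**Step 4: the two effects are one phenomenon.** The Poisson standard error of the log rate ratio is √(1/(75×1.25)+1/(75×1.5)) = 0.140. Adding the one-SD shift at p = 0.4, k = 2 gives √(0.140²+(ln 1.059)²) = 0.151. This is the spread that the unadjusted test treats as 0.140.

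**Step 5: simulation.** p = 0.4, true rate ratio 1, 75 per arm, 3000 runs per scenario, Poisson model with log follow-up as offset, two-sided 5%:

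| k | SD of log rate ratio, without / with AF type | Rejection, without / with AF type |
|---|---|---|
| 1.5 | 0.144 / 0.142 | 5.3% / 5.2% |
| 2 | 0.154 / 0.143 | 7.3% / 4.9% |
| 3 | 0.167 / 0.141 | 9.3% / 4.4% |

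The mean rate ratio is 0.995 to 1.006 in every cell, so neither model is biased. At a true 0.75, both models average 0.748 to 0.752 and reject in 47–49% of runs.

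**The case against.** The strongest reply is that the text does not exclude AF type from the model. A reader might infer that the primary model contains the treatment arm and nothing else. The article says only which effect is tested, and then lists AF type as a covariate in the same paragraph. This stands: the finding is an open role, not a stated unadjusted analysis.

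Three other stronger readings also go beyond the text.

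- **Cardioversion is reserved for patients enrolled with persistent AF.** The sentence in Post-ablation care contains no such restriction. It follows text on recurrence and may describe the rhythm at that time. Nor does that section give a rule for the pre-ablation period, which the endpoint also counts. Baseline type is therefore likely, not certain, to be prognostic.
- **Cardioversion is half of the primary events.** It is one of two named components; no share of events is given.
- **Stratification by AF type is missing.** The article says that patients "will be randomly assigned in a 1:1 ratio". Stratification factors are commonly left to the full protocol. If that document stratifies by AF type, most of the imbalance computed above disappears.

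It is also fair to say that randomisation keeps the unadjusted ratio centred, that little is at stake at k = 1.5, that the 95%-limit shifts are not typical ones, and that adjustment brought no visible gain in power.

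The objection does not remove the point. The article names the model, the test and the covariate list, and only their connection is unsettled.

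**Conclusion.** The point holds in a limited form. The role of AF type in the primary analysis is undetermined, and AF type is the listed covariate most directly tied to a component of the endpoint. If it is left out, there is no systematic bias. The observed rate ratio shifts by about 3–10% per SD of chance imbalance and 7–20% at the 95% limit, against a planned ratio of 0.75. The type I error of the plain Wald test is about 5–10%. These figures rest on an assumed 30–50% persistent, an assumed rate ratio of 1.5 to 3, and allocation not balanced on AF type. At the lower end the effect is close to negligible. The gain from adjustment is a fixed primary analysis, protection against chance imbalance and a test nearer its nominal level. It is not a remedy for power.

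**What to change.** In Statistical analyses, state that the primary Poisson model includes baseline AF type (paroxysmal vs persistent) as a fixed covariate alongside treatment, that the adjusted rate ratio is the single primary result, and that the remaining listed covariates are for subgroup analyses. A robust (dispersion-tolerant) variance can be added for heterogeneity that AF type does not explain.

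The cost is one model term and a sentence or two of text. Every patient's AF type is already known from eligibility, so no new data or patients are needed.

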## Background and rationale

The management of atrial fibrillation (AF) is complex and many patients experience recurrence of symptoms after an invasive treatment with catheter ablation [1]. Although general outcomes of AF ablation have improved over the years, due to innovations of ablation techniques, recurrence of arrhythmias is still experienced by at least one in five patients [2, 3]. The prevalence of AF in Europe is currently estimated at 8 million and is expected to rise to 10 million in a decade [4]. Therefore, more effective therapeutic strategies are required.

Several lifestyle risk factors have previously been identified as promoters of AF. These risk factors include obesity, physical inactivity, sleep apnoea, hypertension, smoking, alcohol use and diabetes mellitus [5–9]. In patients with body mass index (BMI) above 27 kg/m^2^, weight loss and general lifestyle advice leads to cardiac reverse remodelling and a reduction in AF symptom burden [10]. Furthermore, sustained weight loss reverses the natural progression of AF and improves arrhythmia-free survival [11, 12]. Likewise, physical inactivity independently increases the risk of AF [13]. Individuals with better cardiorespiratory fitness have a decreased risk of AF recurrence and experience less severe symptoms [14, 15]. In addition, obstructive sleep apnoea (OSA) has a severe, negative impact on AF treatment. Patients receiving OSA treatment are less likely to progress to more permanent forms of AF [16]. OSA treatment with continuous positive airway pressure (CPAP) significantly decreases AF recurrence rates after pulmonary vein isolation (PVI) [17, 18]. Comparably, beneficial AF outcomes are observed if hypertension is strictly managed, if tobacco use is quitted or if alcohol consumption is decreased [19–21].

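### The primary Poisson Wald test states no allowance for overdispersion, although the endpoint is a per-patient count whose events can cluster

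*Protocol article*

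**What the plan says.** - **Endpoint** (protocol article, Endpoints): "The primary composite endpoint of the study is the number of hospitalizations for re-ablation and cardioversion from baseline to 12 months after ablation". It is a count, so one patient can contribute several events, and events during the wait for ablation are included.
- **How events arise** (Post-ablation care): a symptomatic arrhythmia confirmed more than 3 months after the index procedure leads to an offer of repeat ablation. The section then adds: "Furthermore, patients suffering from persistent AF will undergo cardioversion".
- **Primary test** (Statistical analyses): counts are normalised by participation time, and the arm effect is assessed by "fitting a Poisson regression model to the event data and testing the effect of the intervention group using a Wald test". Rate ratios with 95% confidence intervals follow. No scale parameter, robust variance or negative binomial model is named.
- **Planning rate** (Sample size): "The number of hospital admissions in the control group is estimated as 1.0 per patient per year". No variance or distribution of events per patient is given, and overdispersion is not mentioned.

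**The concern.** Under a Poisson model the standard error of the log rate ratio is computed as if variance equals mean. Two features of this endpoint make that doubtful. One recurrence may generate both a cardioversion and a re-ablation, so events can come in pairs or runs within a patient. The trial also mixes paroxysmal and persistent AF, which differ in how readily a recurrence leads to cardioversion. If events are concentrated in a subset of patients, the Poisson standard error is too small. The primary p value is then too small and the interval too narrow, which raises the risk of a false positive on the trial's one primary comparison.

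**Working it through.** **The plan's own figure.** The article states no dispersion, so there is none to reproduce. The only related figure is the sample size: "the minimum sample size to achieve an 80% power with 5% Type I error on the primary analysis is 144 (72 per treatment group". I checked whether it could contain an allowance for overdispersion, using

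n per arm = phi × (1.96 + 0.8416)² × (1/(1.0·t) + 1/(0.75·t)) / (ln 0.75)²

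With phi = 1 and t = 1 year this is 7.849 × 2.333 / 0.0828 = 221.3, so 222 per arm. It is 178 at t = 1.25 and 148 at t = 1.5. Since phi above 1 only raises n, 72 per arm holds no such allowance. That 72 is not reproduced is a separate matter.

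**Type I error and interval width if phi is not 1.** The Wald statistic is inflated by √phi, so

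type I error = 2 × [1 − Φ(1.96/√phi)]

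| phi (assumed) | 1.96/√phi | Type I error | Interval too narrow by √phi |
|---|---|---|---|
| 1.0 | 1.96 | 5.0% | 1.00 |
| 1.25 | 1.75 | 8.0% | 1.12 |
| 1.5 | 1.60 | 11.0% | 1.22 |
| 2 | 1.39 | 16.6% | 1.41 |
| 3 | 1.13 | 25.8% | 1.73 |

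**When overdispersion is forced.** Let a share p of patients have at least one event and let the mean count be m. For a given p, the mean square is smallest when the affected patients all have the same count, m/p. Hence E[Y²] ≥ m²/p, and

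phi ≥ m(1 − p)/p

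At m = 1.0 (the planned control rate over one year) the bound exceeds 1 whenever p is below 0.5. Because counts are whole numbers, the exact minimum is slightly higher for some p:

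- p = 50%: minimum phi 1.0, type I error 5%
- p = 40%: half of the affected have 2 events and half have 3, so 0.4 × 6.5 − 1 = 1.6, type I error 12%
- p = 30%: two thirds have 3 events and one third have 4, so 0.3 × 11.33 − 1 = 2.4, type I error 21%

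With longer participation the threshold moves up. At 1.25 years (assumed) m = 1.25, and overdispersion is forced below p = 1.25/2.25 = 56%.

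**When it is absent.**

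- If exactly half of patients have one cardioversion plus one re-ablation, the mean is 1.0. With all affected patients having two events, phi = 2(1 − p) = 1.0 and the type I error is 5%.
- If each patient has 0, 1 or 2 events as binomial(2, 0.5), the mean is again 1.0, phi = 0.5 and the simulated type I error is 0.6%.
- With at most one event and p = 0.3, the simulated figure is 1.8%, but the mean is then 0.3, well below the planning rate.

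**Effect of the remedy.** In simulations at 75 per arm with gamma-distributed patient rates, the plain Poisson Wald test at rate 1.0 gave 8%, 12%, 19% and 29% for frailty variances 0.25, 0.5, 1 and 2. Sandwich standard errors gave 4.9% to 6.0% and Pearson-scaled ones 4.7% to 5.4% across the rates tried.

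**The case against.** The strongest reply has two parts.

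First, a Wald test can use a model-based, scaled or sandwich variance. The article does not say which, and a condensed article may leave that to an analysis plan that is not shown. This stands as far as wording goes: the article does not exclude a robust variance. But it names the model and the test for the primary endpoint, and someone following the text as written would run the model-based version. Naming the variance is a concrete improvement to a stated choice.

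Second, nothing in the article establishes overdispersion. A reader might join the planning rate of 1.0 to the background remark that "recurrence of arrhythmias is still experienced by at least one in five patients" and infer that a fifth of patients carry all events, so that the test is badly anti-conservative. The documents do not support that:

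- One in five is a lower bound on recurrence after ablation in general, not a share of patients with an event in this trial.
- Events count from baseline, so a patient with no recurrence after ablation can still contribute a cardioversion from the waiting period.
- At a mean of 1.0, a 20% share would require five procedures per affected patient (1.0/0.20), which nothing in the article suggests.

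This part stands, so severe inflation cannot be asserted as fact.

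A reader might also infer that AF type must be in the primary model for the test to be valid. It need not be. Chance imbalance is already part of sampling error in a randomised comparison, and Statistical analyses already lists AF type among the covariates of interest.

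**Conclusion.** The point holds in conditional form. The stated primary test makes no declared allowance for overdispersion, while the endpoint is one in which events can cluster within patients. If phi lies between 1.5 and 3, the nominal 5% test has a true type I error of about 11% to 26%, and the 95% interval covers about 89% down to 74% (one minus those errors). If most patients have one or two events, the test is near nominal or conservative. If the true event rate is well below 1.0, inflation is smaller: 6% to 13% in the simulations at rate 0.3.

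Phi is an assumption throughout. What follows from the plan's own rate is narrower: at a mean of 1.0, overdispersion is certain if fewer than half of patients have any event. The article does not say what that share is expected to be.

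**What to change.** State in Statistical analyses, before the data are analysed, that the arm effect on the primary endpoint will be tested by Poisson regression with robust (sandwich) standard errors, or by negative binomial regression, with log participation time as offset. Take the confidence interval from the same variance. Choose one of the two in advance. The robust Poisson version keeps the model already named and also corrects the standard error if counts turn out underdispersed, which a negative binomial model does not.

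The change costs one sentence and needs no new data. Its downside is that, with overdispersed counts, the interval widens by √phi and power falls below the plain Poisson value. For 1.0 versus 0.75 at 75 per arm and 1.25 years (assumed), two-sided power is about 45% at phi = 1, 32% at 1.5, 25% at 2 and 18% at 3. The required number per arm at t = 1 rises from 222 to 332, 443 and 664 for the same values of phi. This loss comes from the clustering itself. The plain Poisson analysis would only hide it.
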